## Methods and design

CIFRA is a single arm, single center, open-label, phase II study, assessing the activity of cetuximab in combination with folfiri in FcγRIIIa V/V patients with KRAS, NRAS, BRAF wild type mCRC. It will be conducted at the academic hospital Istituto Nazionale Tumori di Napoli, IRCCS “G. Pascale” in Naples (Italy). The study includes also biomarkers’ analysis (cetuximab-mediated ADCC, TM characterization).

### Objectives

The primary objective is to evaluate the role of the molecular and immunologic selection of patients on response to folfiri and cetuximab in patients with mCRC. The response will be evaluated according to Response Evaluation Criteria In Solid Tumors (RECIST) criteria, version 1.1 [28].

Secondary objectives are the safety, the responses’ duration, the progression-free (PFS) and overall survival (OS). Toxicity will be graded according to the Common Terminology Criteria for Adverse Events (CTCAE) of the National Cancer Institute, version 4.0, June 14, 2010. Response duration will be measured from the time of documented objective response (CR or PR) until documented tumor progression (see also “Response and toxicity assessment” section). PFS will be determined from the data of treatment start untill progression (defined according to RECIST), OS untill death from any cause. Tertiary and correlative objectives consist in exploratory studies of biological markers as predictors of outcome (see the “Tranlsational research” section).

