### Study design and statistical analyses

Sample size is based on a two-stage study design by Simon [29] with activity as primary end-point.

The null hypothesis of a not relevant response rate (40%) will be tested against an alternative response rate hypothesis of 70% with a one-tailed test. The test power is 95%, the alpha value of the I-type error is 5%. With these assumptions the sample for passing the first stage is 14 patients with > 6 objective responses. The final sample is 34 patients with > 18 objective responses to draw positive conclusions.

The populations considered for the analysis are described as follows. Safety Population (SP) is defined as all patients receiving at least one dose of treatment. Incorrect treatment or anticipation of the end of treatment are not reasons for exclusion from the SP. Efficacy Evaluable (EE) population is represented by patients who will receive at least one post-baseline assessment of the primary endpoint [28].

All patients who will receive at least one dose of treatment will be included in the descriptive statistics. The basic characteristics of the recruited patients will be reported for the categorical variables as total number and percentage and for the continuous variables as mean and standard deviation or median and interquartile range. Descriptive statistics of patients excluded from the SP and EE will also be carried out. Summary statistics on treatment will be compiled including information on dose changes, interruptions, non-compliance, reasons for protocol deviation, and treatment duration. The analysis on safety will be carried out on the SP. All the information necessary to identify the occurrence of adverse events will be used in the analysis and summarized through descriptive statistics. The confidence intervals will be calculated at 95%. Time-to-outcome will be described by Kaplan-Meier curves.

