#### End-of-treatment phase

The suspension of the treatment can occur in case of toxicity, progression, and/or at the request of the patient. Additional treatment lines or follow-up procedures will be applied at the discretion of the clinician responsible of the medical treatment. The final visit will be made immediately after disease progression. The following data will be collected: ECOG Performance Status, clinical examination, vital signs, blood count and clinical biochemistry. The end of study visit should be done within 30 days of the last administration of folfiri/cetuximab and before starting any second-line CT. The cutaneous toxicity, if present, will be followed-up until resolution; if second-line CT will be undertaken the treatment will not start before its resolution. In any case, the outcome of adverse events will be recorded after the the end of study visit. The “patient death form” must be completed when the patient dies. The end-of-study form should be completed for patients who die before the end of study visit and if the patient withdraws consent, preferably before 28–32 days after the last folfiri/cetuximab administration.

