### Response and toxicity assessment

The assessment of response will be perfomed through total-body computed tomography with iv contrast (if contraindicated: abdomen MRI and chest computed tomography without iv contrast), CEA and CA19.9 after 3 months of folfiri/cetuximab and every 3 months thereafter until progression. Responses will be classified according to the RECIST v. 1.1. An independent blinded central review of radiologic examinations will be performed by a DMC (Data Monitoring Committee). The independent DMC will be also responsible of reviewing the PFS data. Toxicity will be assessed in accordance with the CTCAE, version 4.0. The CTCAE contains 26 categories of adverse events, organized for pathophysiology, anatomy and etiology. Each adverse event is graded with a scale ranging from 0 (absence of event or value within the normal range) to 5 (death caused by the adverse event). Patients will be assessed for the presence of adverse events at each study visit and will also notify the investigator by telephone in case of significant adverse events reported between one visit and the next. For each adverse event, the maximum grade per patient will be reported. If a patient experiences a toxic effect of any grade on multiple occasions, the event will be counted only once.

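### PFS as defined ends only at RECIST progression, so applied as written it is time to progression and would be overstated to the extent that deaths without documented progression occur

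*Protocol article*

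**What the plan says.** The Objectives section lists PFS, OS and response duration as secondary, together with safety. It defines the first two in one sentence: "PFS will be determined from the data of treatment start untill progression (defined according to RECIST), OS untill death from any cause". On the third it says: "Response duration will be measured from the time of documented objective response (CR or PR) until documented tumor progression".

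Under Study design and statistical analyses, the only method given for these endpoints is: "Time-to-outcome will be described by Kaplan-Meier curves". That section states no event list, censoring rule or competing-risk rule, and it does not say which of its two populations (Safety or Efficacy Evaluable) PFS uses.

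Tumour assessment under Response and toxicity assessment takes place "after 3 months of folfiri/cetuximab and every 3 months thereafter until progression", and the Treatment phase section gives the same timing. The End-of-treatment phase section says treatment may stop for toxicity, for progression or at the patient's request, and adds: "Additional treatment lines or follow-up procedures will be applied at the discretion of the clinician responsible of the medical treatment". It also requires death to be recorded: "The “patient death form” must be completed when the patient dies". Nothing links that form to PFS or response duration.

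**The concern.** Progression-free survival conventionally ends at progression or death, whichever comes first. Here the defining sentence gives PFS one terminating event and reserves death for OS. In a Kaplan-Meier curve whose only event is progression, a patient who dies without it can only be censored, as though still at risk of progressing later. The 3-month scan interval leaves room for such deaths, both before the first scan and between scans.

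The trial has one arm, so its PFS has no concurrent comparator. A reader would probably set it beside figures in the article, such as the 10.0-month median for the cetuximab arm of an earlier phase III trial (Previous results section) or the 18.2-month median for V/V patients in the group's own series (Discussion). The article does not say how death was handled in those figures. A gain produced by the definition alone could be taken for an effect of genotype selection.

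A related uncertainty is whether tumour assessment continues in a patient who stops treatment without progression. The End-of-treatment phase section leaves follow-up procedures to the clinician, while the assessment sections run scans until progression.

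**Working it through.** **1. The plan's own figure.** The only design calculation in the article is the Simon two-stage rule: more than 6 responses in 14, then more than 18 in 34, for 40% against 70%. The probability of a positive result at response rate p is

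Σ (x = 7 to 14) Bin(x; 14, p) × P[Bin(20, p) ≥ 19 − x].

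This gives 0.0385 at p = 0.40 and 0.9507 at p = 0.70, so the stated 5% alpha and 95% power are met. PFS does not enter the calculation, so its definition cannot change it.

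**2. Direction.** The follow-up times are the same under both definitions, and the progression-only version has fewer events. Each Kaplan-Meier factor is therefore equal or larger, and the curve can only stay the same or rise. It stays the same if no patient dies without documented progression.

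**3. Size, as an illustration.** Inputs:

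- True median PFS of 10.0 months, taken from the earlier phase III trial cited in the article.
- Constant hazard (assumption).
- Share f of first PFS events that are deaths without documented progression: 5 to 20% (assumption; the article gives no figure). With all 34 patients having an event, this is 0.05 × 34 = 1.7 to 0.20 × 34 = 6.8, or about 2 to 7 patients.

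The full hazard is λ = ln 2 / 10. Censoring the deaths leaves (1 − f)λ. Hence the reported median is 10 / (1 − f), and the reported 12-month estimate is 0.5^[1.2(1 − f)]. With death counted, the 12-month value is 0.5^1.2 = 43.5%.

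| f | Reported median (months) | Reported 12-month estimate |
|---|---|---|
| 0 (death counted) | 10.0 | 43.5% |
| 5% | 10 / 0.95 = 10.5 | 45.4% |
| 10% | 10 / 0.90 = 11.1 | 47.3% |
| 15% | 10 / 0.85 = 11.8 | 49.3% |
| 20% | 10 / 0.80 = 12.5 | 51.4% |

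**4. Check at the trial's size.** In 4,000 simulated trials per setting (34 patients, same exponential model, assumed cut-off at 24 months), the typical Kaplan-Meier median was 9.5 to 9.6 months with deaths counted. With deaths censored it was 10.3, 10.9, 11.8 and 12.6 months for the four values of f.

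**5. Precision.** With 34 events, an approximate 95% interval for a 10-month median is 10 × exp(±1.96/√34), or 7.1 to 14.0 months.

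**The case against.** **Condensed wording.** A journal article compresses the protocol, the endpoint is called progression-free survival, and censoring rules commonly sit in a fuller document. That is fair as to the censoring rule. It does not cover the definition: the article states the terminating event outright and contrasts it with death in the same sentence. What stands is that censoring is a consequence of following the text, not something the article announces.

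**Early deaths may be excluded, not censored.** If PFS were analysed in the Efficacy Evaluable population, which requires a post-baseline assessment, a patient who dies before the first scan would drop out altogether. Adding death to the definition would not restore that patient. This stands, and it is why the correction must also name the population.

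**Response duration.** A reader might infer that it has the same fault. The text does not support that equally well: the name does not include survival, and a progression-only duration is coherent. The issue there is consistency and clarity.

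**Size.** The 5 to 20% range has no source in the article. Eligibility (ECOG 0 or 1, age under 75, life expectancy over 3 months, no brain metastases) gives no support to the upper end. Shifts of 0.5 to 1.1 months at f = 5 to 10% are small beside an interval of 7.1 to 14.0 months. This stands, although imprecision does not remove a bias of known direction.

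**Follow-up.** A reader might infer that the End-of-treatment phase section contradicts the assessment schedule. Its discretion clause can equally mean care after study treatment, leaving protocol imaging in place. The Duration of therapy section also has patients with toxicity from one drug continue the others until progression, which limits complete stops. This is an ambiguity, not a proven contradiction.

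**Conclusion.** The PFS definition needs correcting. As written, it yields time to progression under the name PFS. The direction of any error is certain, but its size is not: PFS is overstated only to the extent that patients die without documented progression. A true median of 10.0 months would be reported as 10.5 to 12.5 months under a constant hazard if an assumed 5 to 20% of first events are such deaths.

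It would go too far to say that deaths will be censored and PFS will be inflated as a matter of fact, since no such death may occur and the article gives no rate. It would also go too far to say that the trial's conclusion is at risk. PFS is secondary and descriptive, no PFS threshold or test is planned, and the response-rate test and N = 34 are unaffected.

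**What to change.** - Define PFS as the time from treatment start to RECIST progression or death from any cause, whichever is first, in all patients who receive at least one dose. Alternatively, keep the present end-point and rename it time to progression.
- For consistency, count death without progression as an event in response duration, or state that this endpoint is progression-only.
- Reconcile the End-of-treatment phase section with the Treatment phase and Response and toxicity assessment sections, so that it is clear whether tumour assessment continues in patients who stop treatment without progression.

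The cost is a few lines of wording. Deaths are already recorded on a required form, and neither the sample size nor the error rates change. The downside is a slightly shorter reported PFS.

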### Ethical considerations

All the procedures described in this protocol have been designed according to the principles of the Good Clinical Practice guidelines of the International Conference on Harmonization (ICH) and of the Declaration of Helsinki. The study was approved by the Ethical Committee of the National Cancer Institute of Naples, Italy (No. 60/18). All patients will provide a written informed consent to CIFRA study clinicians before recruitment and tissue and blood samples collection. In order to protect the privacy of patients included in the CIFRA study, the Structure that has the responsibility for registration, collection and management of personal data, will not provide patient names to persons not involved in the study, with the exception of the Ministry of Health or Ethics Committees (as required by the current legislation only for inspection and control purposes). After registration, a unique and progressive numerical code will be assigned to the patients and shown in the header of all electronic data collection systems and it will be used for all communications regarding the patients. A list of patients’ codes will exist exclusively at the Secretariat of the CIFRA study.

### Study design and statistical analyses

Sample size is based on a two-stage study design by Simon [29] with activity as primary end-point.

The null hypothesis of a not relevant response rate (40%) will be tested against an alternative response rate hypothesis of 70% with a one-tailed test. The test power is 95%, the alpha value of the I-type error is 5%. With these assumptions the sample for passing the first stage is 14 patients with > 6 objective responses. The final sample is 34 patients with > 18 objective responses to draw positive conclusions.

The populations considered for the analysis are described as follows. Safety Population (SP) is defined as all patients receiving at least one dose of treatment. Incorrect treatment or anticipation of the end of treatment are not reasons for exclusion from the SP. Efficacy Evaluable (EE) population is represented by patients who will receive at least one post-baseline assessment of the primary endpoint [28].

All patients who will receive at least one dose of treatment will be included in the descriptive statistics. The basic characteristics of the recruited patients will be reported for the categorical variables as total number and percentage and for the continuous variables as mean and standard deviation or median and interquartile range. Descriptive statistics of patients excluded from the SP and EE will also be carried out. Summary statistics on treatment will be compiled including information on dose changes, interruptions, non-compliance, reasons for protocol deviation, and treatment duration. The analysis on safety will be carried out on the SP. All the information necessary to identify the occurrence of adverse events will be used in the analysis and summarized through descriptive statistics. The confidence intervals will be calculated at 95%. Time-to-outcome will be described by Kaplan-Meier curves.

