**Methods/design:**

CIFRA is a single arm, open-label, phase II study assessing the activity of cetuximab in combination with irinotecan and fluorouracile in FcγRIIIa V/V patients with KRAS, NRAS, BRAF wild type mCRC. The study is designed with a two-stage Simon model based on a hypothetical higher response rate (+ 10%) of FcγRIIIa V/V patients as compared to previous trials (about 60%) assuming ADCC as one of the possible mechanisms of cetuximab action. The test power is 95%, the alpha value of the I-type error is 5%. With these assumptions the sample for passing the first stage is 14 patients with > 6 responses and the final sample is 34 patients with > 18 responses to draw positive conclusions. Secondary objectives include toxicity, responses’ duration, progression-free and overall survival. Furthermore, an associated translational study will assess the patients’ cetuximab-mediated ADCC and characterize the tumor microenvironment.

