### The current therapeutic context of mCRC and CIFRA hypothesis

Recent meta-analyses [24, 25] have evidenced the role of colon tumor side (rigt vs left) as a predictive factor for response to therapy [26]. Accordingly, the RAS wt tumors deriving from the left colon would be more responder to CT in association with anti-EGFR drugs as compared to the right-sided neoplasms. However, the treatment of the RAS wild-type mCRC is currently based on the use of CT doublets (fluoropyrimidine and oxaliplatin or irinotecan) and biological drugs (bevacizumab, panitumumab, cetuximab). This concept is well expressed in the ESMO (European School of Medical Oncology) guidelines [27] in relation to the diversity of the initial treatment intent, suggesting the use of CT doublets and anti-EGFR (panitumumab or cetuximab) when the main objective is a rapid tumor shrinkage. The NCCN guidelines (National Comprehensive Cancer Network v3.2018) contemplate the use of CT and anti-EGFR, panitumumab or cetuximab, in first or second line therapies in mCRC patients whose primary tumor is localized to the left colon. At present, however, due to a lack of sequence studies with high cross-over rates between biologic drugs, it is not possible to state the best biological drug to be used in first-line.

Here we propose the administration of folfiri (fluorouracile and irinotecan) plus cetuximab in patients selected on the FcγRIIIa V/V genotype. In summary, the CIFRA study is set on a hypothetical higher response rate of FcγRIIIa V/V patients than those reported in previous trials (about 60%) and assumes that ADCC is one of the possible mechanisms of cetuximab action. Furthermore, in this immunologically selected cohort, the different responses associated to tumor side (right vs left) could be non existent or attenuated. CIFRA study results could contribute to ameliorate patients’ selection and definitively address the ADCC and FcγR polymorphisms role in cetuximab activity.

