## Discussion

The identification of predictive biomarkers characterizing the ideal treatment of mCRC patients is subject of intense investigation. RAS oncogenes in mCRC have not completely satisfied this unmet need since about 40% of patients with RAS wt mCRC dose not respond to anti-EGFR treatments. We previously reported in a series of 74 KRAS wt mCRC patients, genotypic frequencies of FcγRIIIa and FcγRIIa of 36% VV, 54% VF, 10% FF and 36% HH, 56% HR, 8% RR, respectively; interestingly, FcγRIIIa but not FcγRIIa polymorphisms were significantly associated with response to anti-EGFR-based therapy [20]. FcγRIIIa polymorphisms had also significant prognostic value for PFS [FcγRIIIa: median PFS 18.2 months in V/V patients (18 patients, 13 events) vs 17.3 months in V/F patients (26 patients, 25 events) vs 9.4 months in F/F patients (5 patients, 5 events); Log Rank test: *p* = 0.04] at univariate and multivariate analyses (HR: 2.35; CI: 1.37–4.01; *p* = 0.001) with grading and response to first-line chemotherapy. In another study, we described genotipic frequencies of FcγRIIa and IIIa in 96 consecutive mCRC patients and 148 control subjects and we analyzed the clinical impact of cetuximab-mediated ADCC in vitro from LAK patients-derived [21]. There were no statistically significant differences between the control and study groups in terms of genotypic frequencies. The incidence of FcγRIIIa V/V, V/F and F/F were: 28, 47 and 23%, respectively. Interstingly, the FcγRIIIa V/V and V/F genotypes were associated with higher cetuximab-mediated ADCC compared with F/F, median 27% (range: 0–76%) and 20% (0–57%) versus 9% (0–36%), respectively (*p* = 0.001). The response rate was higher in patients with the FcγRIIIa V allele (*V/V and V/F* genotypes) compared with the F/F genotype (*p* = 0.025) as well as the PFS of patients with FcγRIIIa V/V and V/F was significantly longer than that of patients with F/F (10.8 vs. 5.1 months respectively, *p* = 0.05, Log Rank test). The extent of in vitro cetuximab-mediated ADCC was significantly correlated with cetuximab clinical response (30% in responders vs 8% in non-responders patients, *p* = 0.020; ANOVA test). These observations prompted us to prospectively design the CIFRA trial, which is an investigator initiated phase II study to verify a superior activity of folfiri/cetuximab of 70% (+ 10% of that previously described) in mCRC patients selected on a genetic polymorphism of FcγRIIIa. The risk of a possible unexpected detrimental effect in this selected population is reduced in CIFRA study by the two-stage design that will stop the enrollment early if the first condition of acceptable activity is not met.

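### The Simon rule tests a 40% response rate, but the article presents the trial as verifying a gain over about 60%; if 60% applies to this population and V/V selection adds nothing, the trial is still positive about 70% of the time

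*Protocol article*

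**What the plan says.** The protocol article states the design under 'Study design and statistical analyses': "Sample size is based on a two-stage study design by Simon [29] with activity as primary end-point". The hypotheses follow: "The null hypothesis of a not relevant response rate (40%) will be tested against an alternative response rate hypothesis of 70" per cent, "with a one-tailed test". The error rates are given as "The test power is 95%, the alpha value of the I-type error is 5" per cent. The trial passes stage 1 with more than 6 responses in 14 patients, and it needs more than 18 in 34 "objective responses to draw positive conclusions".

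Three other places describe a different comparison:

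- Abstract, Methods/design: the two-stage model is said to rest on a response rate 10 points higher in V/V patients "as compared to previous trials (about 60%) assuming ADCC as one of the possible mechanisms of cetuximab action". The abstract then gives the same error rates and boundaries as the consequence of these assumptions. It does not mention 40%.
- 'The current therapeutic context of mCRC and CIFRA hypothesis': the study is set on a higher rate in V/V patients "than those reported in previous trials (about 60" per cent).
- Discussion: the trial was designed "to verify a superior activity of folfiri/cetuximab of 70" per cent, glossed as 10 points above what had been described before.

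The Objectives section makes the role of molecular and immunologic selection in the response the primary objective. The section on earlier folfiri plus cetuximab results reports 59.3% and 62.0% (95% CI 56.2 to 67.5) in KRAS wild-type patients, and 43.2% for chemotherapy alone. The trial has a single arm.

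**The concern.** The 5% error rate protects a conclusion only against the null that was tested. Here that null is 40%, while the comparison offered to the reader is with about 60%. With no control arm, the benchmark is the only thing that could connect the result to a gain from patient selection, and the decision rule does not use it.

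A positive CIFRA could therefore be read as showing that V/V patients respond better than unselected patients, when the test shows only that the rate exceeds 40%. The Discussion already looks ahead to a pilot study in RAS-mutated V/V patients and to phase III trials that CIFRA might prompt. A reader of the abstract alone would also believe that 34 patients suffice to tell 70% from 60% with 95% power.

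**Working it through.** **Inputs.** From the design section: p0 = 0.40, p1 = 0.70, one-sided alpha 0.05, power 0.95, n1 = 14, r1 = 6, n = 34, r = 18. From the abstract, hypothesis section and Discussion: benchmark about 0.60. From the section on earlier results: 0.593 and 0.620. The 55% row in the table is an assumed value, included to show sensitivity.

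**Formula.** The trial is positive if X1 ≥ 7 in the first 14 patients and the total is at least 19 of 34:

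P(positive | p) = Σ (x1 = 7 to 14) Bin(x1; 14, p) × P[Bin(20, p) ≥ 19 − x1]

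**Step 1: reproduce the plan.** At p = 0.40 the result is 0.0385, and at p = 0.70 it is 0.9507. A search over two-stage designs for 40% versus 70% with 5% and 95% returns 6/14, 18/34 as Simon's optimal design. The arithmetic is right for the hypotheses in the design section.

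**Step 2: same rule at the benchmark.** At p = 0.60 the terms for x1 = 7, 8, …, 14 are 0.0938, 0.1561, 0.1803, 0.1462, 0.0827, 0.0315, 0.0073 and 0.0008. They sum to 0.699.

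| True response rate | P(stop at stage 1) | P(positive) |
|---|---|---|
| 40% (tested null) | 0.692 | 0.038 |
| 55% | 0.259 | 0.483 |
| 59.3% (first cited trial) | 0.163 | 0.671 |
| 60% (stated benchmark) | 0.150 | 0.699 |
| 62.0% (second cited trial) | 0.116 | 0.772 |
| 70% (alternative) | 0.031 | 0.951 |

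**Step 3: smallest positive result.** 19/34 = 55.9%, which is below 59.3%, 60% and 62.0%. Its exact 95% interval is 37.9% to 72.8%.

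**Step 4: what 34 patients can do against 60%.** Keep stage 1 and raise the final cut-off until P(positive | 0.60) ≤ 0.05:

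- more than 24/34 gives 0.073, which is too high;
- more than 25/34 gives 0.034, with P(positive | 0.70) = 0.268.

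Power for 60% versus 70% at one-sided 5% is therefore about 27%.

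**Step 5: size needed for 60% versus 70%.** For an exact single-stage binomial test at one-sided 5%, taking the first n that meets the target:

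- n = 143, at least 96 responses: alpha 0.0477, power 0.800;
- n = 248, at least 162 responses: alpha 0.0490, power 0.952.

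The premise in the abstract does not lead to 34 patients.

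**The case against.** The strongest reply is that the design section is valid on its own terms. It names 40% as a rate of no interest, names activity as the endpoint, and uses the optimal Simon design for that question. A null at an inactivity floor with the target as the alternative is a common phase II screen. The Discussion also gives the two-stage rule the purpose of stopping early for an unexpected detrimental effect, which fits a floor below 60%. This stands: neither the alpha nor the sample size is miscalculated. It does not remove the conflict, because the other sections present the result as a comparison with about 60%, and the abstract derives the boundaries from that comparison.

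The planned 95% confidence intervals are a partial safeguard. At 19/34 the interval plainly includes 60%. That limits misreading but does not change what the rule declares positive.

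The figure of about 70% is conditional, and this also stands. It assumes that 60% would be the rate in this population without any V/V effect. The figure falls to 0.48 at 55%. It would rise if the additional NRAS and BRAF wild-type selection lifts the rate by itself.

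Three stronger readings are tempting, and the document does not support them:

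- A reader might infer that the cited trials have already refuted the 40% null. Those trials are reported for KRAS wild-type patients. CIFRA adds NRAS, BRAF and V/V selection, omits irinotecan at the first administration and uses independent blinded review. The cited rates make 40% an undemanding null, and no more than that.
- A reader might infer that the article says outright that more than 18/34 verifies a 10-point gain. No sentence does. The boundary and the superiority aim stand in different sections, and the link is an inference that the wording invites.
- A reader might take 26/34 or more as evidence of exceeding 60%. The exact 95% interval at 26/34 is 58.8% to 89.3%, which includes 60%. The error of that cut-off is 5.6% if the benchmark is the cited 62.0%. Without a comparator, no cut-off separates a V/V effect from NRAS and BRAF selection.

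**Conclusion.** The point holds as a mismatch between the test and the claim attached to it. The Simon rule is correct for 40% versus 70%, and the 5% and 95% apply to that pair only. Measured against the article's own benchmark, a trial in which V/V selection adds nothing would be declared positive with probability about 0.70, or 0.67 to 0.77 across the two cited rates. This assumes that the benchmark carries over to this population and that the boundaries mean strictly more than 6 and strictly more than 18, as printed. A positive result would show activity above 40%. It would not show superiority over about 60% or an effect of V/V selection. The conflict lies within the printed text, so a separate analysis plan would not remove it.

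**What to change.** Keep the 34 patients and the go/no-go rule, and change the wording:

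1. In the abstract, state the 40% null. There and in the design section, say that the 5% error and 95% power apply only to 40% versus 70%, and that the probability of a positive result is about 0.70 if the true rate is 60%.
2. In the design section, limit the conclusion from more than 18/34 to activity above 40%. Reword the abstract, the hypothesis section and the Discussion so that a positive result is not presented as verifying superiority over about 60% or an effect of V/V selection.
3. Report the response rate with its 95% confidence interval beside the 60% benchmark, labelled as descriptive. State that 34 patients give only about 27% power for 60% versus 70% at one-sided 5%, and that an exact single-stage test would need about 143 patients for 80% power or 248 for 95%.

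This takes no extra patients and no change to the conduct of the trial. The price is a more modest claim.
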